**STUDY PROTOCOL – DOMS RECOVERY TRIAL**

**Study Design and Setting**

A randomized, controlled, double-blind trial involving young athletes will be performed. The Helsinki ethical guidelines will be followed, and all the participants after receiving a presential explanation of the study’s procedure will complete an informed consent form before starting the study.

Participants will be allocated into one of four distinct groups: the Control group (Cont), which received no intervention; the Super Induction group (P); the Transcranial group (T); and the Combination of Stimulation group (Comb). A neutral location will be designated for administering the treatments, and researchers assigned to the treatment stations will be exclusively involved in administering the interventions.

**Sample size calculation**

The sample size calculation for the study has been performed using G*Power Software. An F-test was selected for an ANOVA with repeated measures, accounting for within-between interaction. Input parameters included a medium effect size f=0.20, a significance level of 0.05, a power of 0.8, four groups, five measurements, and a nonsphericity correction of 1. The results indicated that a total sample size of 48 participants is required to achieve the sufficient statistical power. To account for potential losses of 10%, the sample size will be increased to 52 participants (13 per group) to compensate for possible dropouts.

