**Statistical analysis**

SPSS v.29 (IBM, Armonk, NY, USA) will be used to perform statistical analysis. Normal distribution of data will be assessed using histograms and the Shapiro-Wilk test. Variables with a p-value less than <0.05 will be considered to have a non-normal distribution, while variables with a p-value greater than 0.05 will be considered to have a normal distribution. To describe the sample, the mean and standard deviation will be reported for normally distributed variables, while the median and interquartile range will be reported for non-normally distributed variables. Independent t tests or Mann-Whitney U tests will be used to compare means between groups at baseline for quantitative variables. When the assumptions are met, a 5x4 (5 measurements x 4 groups) mixed analysis of variance (ANOVA) will be performed, with correction for multiple comparisons using the Bonferroni test. The effect size, expressed as partial eta squared (ηp2​), can be categorized into three ranges: a small effect (0.01), a medium effect (0.06), and a large effect (0.14).

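### The 48 reproduces, but 52 does not cover 10% loss, f = 0.20 is not the protocol's own medium effect, and epsilon = 1 leaves little margin for the stated power

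*Protocol*

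**What the plan says.** All the inputs stand in the protocol under Sample size calculation. The test is a repeated-measures interaction test: "An F-test was selected for an ANOVA with repeated measures, accounting for within-between interaction". The settings are given as: "Input parameters included a medium effect size f=0.20, a significance level of 0.05, a power of 0.8, four groups, five measurements", together with "a nonsphericity correction of 1". The result is a total of 48, which is then raised: "To account for potential losses of 10%, the sample size will be increased to 52 participants (13 per group").

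Under Statistical analysis, the protocol plans a 5 x 4 mixed ANOVA in SPSS and expresses effects as partial eta squared, which "can be categorized into three ranges: a small effect (0.01), a medium effect (0.06), and a large effect (0.14").

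Under Procedure, the five readings are one before the damaging exercise and four at 1, 24, 48 and 72 hours after it.

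**The concern.** A reader will take the trial to have 80% power for a medium effect, with 10% loss already allowed for. Each part of that reading needs checking.

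- **Loss.** Ten per cent of 52 is more than the four participants added to 48.
- **Effect label.** The sample-size section and the analysis section use the word medium on two scales that do not agree.
- **Sphericity.** The power is computed at the upper limit of epsilon, although the readings are unevenly spaced around an acute insult.

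If the interaction turns out non-significant, these statements decide how strongly the result counts against a medium effect.

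**Working it through.** **Inputs.** From the protocol: f = 0.20, alpha = 0.05, k = 4 groups, m = 5 measurements, epsilon = 1, N = 48, inflated N = 52, loss 10%, medium = partial eta squared 0.06. Assumed, because the protocol does not give it: correlation among repeated measures, rho = 0.5, with other values shown below.

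**Step 1. Reproduce the 48.** G*Power's default form for the within-between interaction is

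- lambda = f² × N × m × epsilon / (1 − rho)
- df1 = (k − 1)(m − 1) × epsilon
- df2 = (N − k)(m − 1) × epsilon

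At N = 48: lambda = 0.04 × 48 × 5 / 0.5 = 19.2, df1 = 12, df2 = 44 × 4 = 176. Power is 0.821. At N = 44 it is 0.775. With equal groups, 48 is therefore the smallest size that reaches 0.80, and the stated figure reproduces. It also pins the correlation: with equal groups, f = 0.20 returns 48 only for rho of about 0.48 to 0.52. Rho 0.4 would return 56 and rho 0.6 would return 40.

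**Step 2. Loss.**

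- 52 × 0.9 = 46.8 completers, below 48.
- Inflation by division: 48 / 0.9 = 53.3, so 54, or 56 in equal groups.
- Inflation by multiplication: 48 × 1.1 = 52.8, so 53.
- What 52 covers: 52 − 48 = 4 losses, and 4 / 52 = 7.7%.

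Power under the plan's own settings is 0.799 at 46 completers and 0.810 at 47.

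**Step 3. Effect label.** The conversion is f = √(η² / (1 − η²)).

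- Partial eta squared 0.06 gives f = √(0.06 / 0.94) = 0.253.
- f = 0.20 gives 0.04 / 1.04 = 0.038, below the medium mark.

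That is the direct conversion. The G*Power default f, however, enters lambda together with the correlation, so it is not on the scale of the partial eta squared that SPSS prints. On that scale the powered effect is

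- 19.2 / (19.2 + 176) = 0.098, using the error degrees of freedom (SPSS form), or
- 19.2 / (19.2 + 192) = 0.091, using N(m − 1) = 192 (Cohen form).

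Both lie above the medium mark. A true 0.06 at N = 48 has

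- SPSS form: lambda = (0.06 / 0.94) × 176 = 11.2, power 0.53
- Cohen form: lambda = (0.06 / 0.94) × 192 = 12.3, power 0.58

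**Step 4. Sphericity.** Power at N = 48 and f = 0.20. The epsilon values below 1 are assumptions, since the protocol gives no data from which to derive one.

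| rho | epsilon 1 | 0.9 | 0.75 | 0.6 |
|---|---|---|---|---|
| 0.3 | 0.64 | 0.61 | 0.55 | 0.48 |
| 0.5 | 0.82 | 0.79 | 0.73 | 0.65 |
| 0.6 | 0.91 | 0.89 | 0.84 | 0.76 |
| 0.7 | 0.98 | 0.97 | 0.94 | 0.89 |

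At rho 0.5, power crosses 0.80 at epsilon of about 0.94.

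**The case against.** The strongest defence is that the main figure is right: 48 reproduces, and 47 would already suffice without equal groups. **This stands.** It would be wrong to infer that the sample-size calculation as a whole fails. It would also be wrong to infer that 10% loss costs the trial its power, because 46 or 47 completers still give about 80%.

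Second, a reader might conclude that 80% power holds only under exact sphericity. **The documents do not support that.** The threshold at rho 0.5 is near 0.94, not 1. A higher true correlation would offset a lower epsilon, and if all 52 complete, epsilon 0.9 still gives 0.83. No epsilon can be derived from the protocol: uneven spacing makes departure from sphericity a fair worry, but does not measure it. The protocol also makes the mixed ANOVA conditional on its assumptions being met, and how sphericity is tested or corrected may be set out in an analysis plan that is not at hand. Against this, a correlation of 0.6 or 0.7 is not what the plan's own 48 implies.

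Third, on direct conversion the label errs on the safe side: f = 0.253 in the same formula has power 0.97 at 48. **This stands for that reading.** The unfavourable reading requires that f be the G*Power default and that the medium band refer to the SPSS output. The reproduction of 48 supports the first, and the choice of SPSS and partial eta squared makes the second natural, but the protocol does not link the two scales. The readings should not be combined by taking 0.038 from one and testing it on the other.

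**Conclusion.** The point holds in a limited form. The 48 is correct under its inputs and a correlation of about 0.5.

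1. **The 10% claim is wrong arithmetically.** The shortfall is 1 to 2 participants, or 4 for equal groups, with negligible effect on power.
2. **The word medium contradicts the analysis section on either reading.** The powered effect is 0.038 by direct conversion, or about 0.09 to 0.10 on the reported scale. Only the second reading harms interpretation: power for a true 0.06 is then about 0.53 to 0.58.
3. **Epsilon 1 leaves little margin.** At rho 0.5 and 48 completers, power is 0.79, 0.73 and 0.65 at assumed epsilon 0.9, 0.75 and 0.6. How much is lost depends on the true correlation, in both directions.

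Confidence is high for the loss arithmetic and the label mismatch. It is lower for the size of the power loss, which rests on an inferred correlation, assumed epsilon values and an inferred effect-size convention.

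**What to change.** Keep 52 and revise the sample-size paragraph:

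- State that 52 allows for 4 losses (7.7%) while retaining 48.
- Remove the word medium, or give the equivalent of f = 0.20 on the partial eta squared scale used in the analysis section and say which conversion applies.
- State the correlation and the definition of f that were entered in G*Power.
- Report power at 48 over a range of epsilon, for example 0.6 to 1.0 (0.65 to 0.82 at correlation 0.5), labelled as an assumption.

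The cost is wording only, with no additional participants. The drawback is that the stated power will look less favourable than it does now.

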**Participants**

The research will be conducted with participants from a university, selected based on specific inclusion and exclusion criteria to ensure the relevance of the study results. Recruitment efforts will be implemented through communication channels and advertisements strategically placed within the Faculty of Sports Sciences of the university.

The inclusion criteria will be males aged between 18 and 35 years; engaged in regular physical activity at least three times a week for a minimum duration of one year; and exhibiting no hypersensitivity in areas to be treated with peripheral stimulation. Exclusion criteria will be not to have been diagnosed with any chronic disease; not to have sustained a musculoskeletal injury to the lower extremity within the preceding six months; and not to be smokers.

**Randomization**

Randomization of groups will be performed using the randomization function of Microsoft Office Excel (Microsoft Corporation, Redmond, Washington, USA). Participants will be assigned to one of four study groups as described previously. The examiners and the data analyst will be blinded to the participant’s group allocation during the study as a special room will be designed for the participants to receive the treatments.

**Procedure**

The study's methodology will involve a structured series of five assessment sessions for each participant. A familiarization session will be conducted one week prior to the commencement of the first assessment to acquaint participants with the procedures and equipment.

The assessment session (T1) will be comprehensive, encompassing a range of physiological and biomechanical measurements, such as the collection of creatine kinase (CK) levels, blood lactate concentration, performance in the Counter Movement Jump (CMJ), dynamometry of the quadriceps, surface electromyography (EMG) of the quadriceps, and anthropometric data.

Subsequent sessions will be scheduled at specific intervals post-exercise - namely 1 hour (T2), 24 hours (T3), 48 hours (T4), and 72 hours (T5) after the induction of muscle damage - to track the progression and recovery over time.

The evaluation of muscle damage will be primarily focused on the analysis of blood CK and lactate concentrations, obtained from a pin prick blood samples and will be analyzed using electrophoretic analysis (Lactate Scout Pro, Musimedic S.L Donostia, Spain). To ensure the accuracy of these enzyme measurements, participants will be instructed to abstain from any physical activity for at least two days prior to the study, before the baseline timeline (T1 study time). The participants could resume a normal physical activity after completing the first day (including T1 and T2 study time).

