***Protocol for Transcranial and Peripheral Electromagnetic Stimulation in the Study***

Control (Cont) Group: The electromagnetic stimulation machine will be positioned identically as in the active treatment groups. However, the machine will be turned off, and pre-recorded sounds of the machine's operation will be playing during the treatment session.

Super Inductive (P) Group: The PES treatment will be administered, following the Long-Term Potentiation protocol. This protocol will entail five stimulations at 100 Hz, each lasting for 5 seconds, interspersed with 55-second rest intervals. The total stimulation time for this group will be 10 minutes.

Transcranial Stimulation (T) Group: This group will receive TES treatment involving 2000 pulses administered over a minimum duration of 20 minutes, targeting the cortical area M1.

Combined Stimulation (Comb) Group: Participants in this group will receive a combination of both PES and TES treatments, with the total stimulation time extending to 30 minutes.

In all groups, the treatment will start one hour post the eccentric exercise session, aligning with the onset of fatigue, time T2 in the study.

The TES and PES treatments will be administered using a MagRex magnetic stimulator equipped with a ring-shaped coil / 8-shaped coil (MR Inc., Republic of Korea, http://www.mrev.co.kr).

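### Blood lactate is named with CK as a main marker of muscle damage, but at the sessions clearly after treatment (24, 48 and 72 h) it can carry no trace of the exercise

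*Protocol*

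**What the plan says.** All of this is in the protocol.

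- **Role of lactate (Procedure).** "The evaluation of muscle damage will be primarily focused on the analysis of blood CK and lactate concentrations". The next sentence, which introduces the two-day abstention from exercise, begins "To ensure the accuracy of these enzyme measurements" and so treats both analytes as enzymes.
- **Sampling.** Lactate is listed by name in the T1 battery, before exercise. The later sessions are at set times, "namely 1 hour (T2), 24 hours (T3), 48 hours (T4), and 72 hours (T5) after the induction of muscle damage", and their purpose is "to track the progression and recovery over time". No session falls during or straight after the exercise.
- **Treatment (Protocol for Transcranial and Peripheral Electromagnetic Stimulation in the Study).** "In all groups, the treatment will start one hour post the eccentric exercise session". The same sentence identifies that moment with T2.
- **Activity between sessions (Procedure).** Normal physical activity may resume once the first day, with T1 and T2, is complete.
- **Declared outcomes.** Surface EMG is primary. Dynamometry and the counter movement jump stand under the secondary heading. Lactate appears under neither.

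**The concern.** A marker of damage and recovery has to change with damage, and to do so at the times when it is measured. The session times suit a process that develops over one to three days. Lactate rises with effort and falls again within the hours after it. One of the two blood markers on which the protocol rests its evaluation of damage would therefore be read at times when it has nothing to say about the exercise session.

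What is at stake is interpretation. A flat lactate curve from T3 to T5 could be taken as recovery, or as absence of a treatment effect, when it would look the same whatever the damage. A difference between groups at those sessions could come from chance or from what participants did that day, since activity is not restricted after day 1. The word enzyme adds a further doubt about whether lactate was the intended analyte.

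**Working it through.** The protocol gives no lactate figure to reproduce, and neither its sample size calculation nor its statistical analysis section names lactate. The check is one of timing.

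**Inputs from the protocol**
- Sessions after exercise: 1, 24, 48 and 72 h (Procedure).
- Start of treatment: 1 h after exercise, at T2 (stimulation section).
- Participants: 52 randomised, 48 required by the calculation (Sample size calculation).

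**Assumptions, not in the protocol**
- Lactate reflects recent effort and the exercise rise decays exponentially with half-life *h*.
- *h* is 10 to 40 min for the 1 h reading. It is extended to 60 min at 24 h and later, to be generous to the marker.

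**Formula.** Share of the exercise rise remaining at time *t* = 0.5^(*t*/*h*).

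**At T2, *t* = 60 min**

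| *h* (min) | Calculation | Share left |
|---|---|---|
| 10 | 0.5^6 | 1.6% |
| 15 | 0.5^4 | 6.3% |
| 20 | 0.5^3 | 12.5% |
| 30 | 0.5^2 | 25% |
| 40 | 0.5^1.5 | 35% |

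So lactate may still be raised at T2. What remains depends on how high the exercise drove it and how fast the participant clears it, at a moment when treatment is only starting.

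**At T3 to T5**

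| Session | *h* = 40 min | *h* = 60 min |
|---|---|---|
| 24 h | 0.5^36 = 1.5 × 10^-11 | 0.5^24 = 6.0 × 10^-8 |
| 48 h | smaller still | 0.5^48 = 3.6 × 10^-15 |
| 72 h | smaller still | 0.5^72 = 2.1 × 10^-22 |

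For an assumed rise of 14 mmol/L and *h* = 60 min, the remainder at 24 h is 14 × 6.0 × 10^-8 = 8.4 × 10^-7 mmol/L, which is zero for practical purposes.

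**How wrong would the half-life have to be?** For 1% of the rise to remain at 24 h, *h* = 24 / log2(100) = 24 / 6.64 = 3.6 h. That is 3.6 times the top of the assumed range.

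**Number of readings concerned, if lactate is taken at T3, T4 and T5.** 52 × 3 = 156 with no losses, or 48 × 3 = 144 with 48 completers.

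**The case against.** The strongest reply is that lactate carries little weight in this trial. It is not a declared outcome, so a weak ancillary marker does not bias the EMG, dynamometry or jump comparisons. This stands. A reader might infer that the main result is compromised, or that the protocol commits itself to testing lactate in the 5x4 mixed ANOVA. The documents support neither: the Statistical analysis section does not say which variables enter that model.

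Serial sampling is also inferred. Lactate is named only in the T1 list. Repeated sampling is the natural reading, because a single value before exercise could not evaluate damage at all, but the protocol has no visit-by-visit list. The point is conditional on it.

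A reader might further infer that lactate has cleared by every session after exercise. That is too strong, because up to about a third of the rise may remain at 1 h. Nor does the protocol say whether the T2 assessment precedes the stimulation, so T2 cannot be called strictly pre-treatment. This does not rescue the marker. If blood were drawn after stimulation instead, the draw would come later where the session is longer (10 min in the P group, 30 min in the Comb group). Groups could then differ through clearance time alone: with *h* = 30 min, 0.5^(70/30) = 20% against 0.5^(90/30) = 12.5%.

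Nor is lactate unable to move at T3 to T5. It can move with that day's activity, but such movement says nothing about damage.

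Finally, the half-life and the view of lactate as a marker of effort come from general physiology, not from the protocol. They are stated as assumptions, and the result at 24 h does not depend on the exact value.

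**Conclusion.** The point holds for T3 to T5. The protocol gives lactate a damage-marker role that it cannot fill at the sessions clearly after treatment: at most 6 × 10^-8 of the exercise rise remains at 24 h for any half-life from 10 to 60 min. At T2 about 2% to 35% may remain (half-life 10 to 40 min), and it reflects exercise effort. Calling lactate an enzyme measurement is a plain error in the text.

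The conclusion rests on lactate being sampled at each session and on the assumed clearance. It does not reach CK, the primary outcome or the listed secondary outcomes. The change is worth making before the blood results are interpreted, but the trial's main comparison does not depend on it.

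**What to change.** In the Procedure section:

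1. Remove lactate as a marker of muscle damage, recovery or treatment effect, and rest the blood evaluation of damage on CK.
2. State that no between-group conclusion about damage will be drawn from lactate at T2 to T5.
3. Correct the reference to enzyme measurements so that it covers CK only. If another enzyme was meant in place of lactate, name it.
4. Do not keep the 1 h reading as a description of exercise intensity. By the figures above, 65% to 98% of the rise has gone by then.

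One consequence needs attention. The section names a single analyser, the Lactate Scout Pro, for both analytes. Once CK stands alone, the text should say how CK is measured.

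The cost is wording, plus one fewer blood marker to report. The finger prick for CK continues. If lactate sampling at T3 to T5 is dropped as well, 144 to 156 readings are saved.

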**Primary Outcome Measure: Surface Electromyography**

In this research, the mDurance® EMG system (mDurance Solutions SL, Granada, Spain) will be employed. This portable surface EMG (sEMG) system integrates three components: sensors, mobile computing, and a cloud-based data analysis framework.

1. First Sensor – Rectus Femoris (RF) Evaluation: Participants will be positioned on a stretcher, with knees slightly flexed and the trunk leaning backwards. Electrodes will be placed at the midpoint between the anterior superior iliac spine (AIS) and the top of the patella. The ground electrode will be positioned on the patella.

2. Second Sensor – Vastus Lateralis (VL) and Vastus Medialis (VM) Activity Recording: For the VE, electrodes will be positioned at two-thirds of the distance along the line from the EIAS to the lateral part of the patella. For the VM, electrodes will be placed at 80% of the distance from the EIAS to the anterior border of the internal lateral ligament.

Surface muscle activity will be captured using two bipolar sensors provided by Shimmer Research Ltd, Dublin, Ireland. Data recording and transmission will be facilitated by the mDurance® mobile application, installed on a Galaxy A7 Android Tablet (ZtotopCase, Suwon, South Korea).

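### Exercise is restricted before T1 but allowed, and not recorded, before T3, T4 and T5, leaving the post-treatment readings open to the effects of new activity

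*Protocol*

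**What the plan says.** All statements are in the protocol; no SAP was available.

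- **Before T1** (Procedure): "participants will be instructed to abstain from any physical activity for at least two days prior to the study". The reason given is "To ensure the accuracy of these enzyme measurements", which refers to creatine kinase (CK) and lactate.
- **After day 1** (Procedure, the next sentence): "The participants could resume a normal physical activity after completing the first day (including T1 and T2 study time".
- **Follow-up visits** (Procedure): they are set at fixed times, "namely 1 hour (T2), 24 hours (T3), 48 hours (T4), and 72 hours (T5) after the induction of muscle damage", and their purpose is "to track the progression and recovery over time".
- **Who is enrolled** (Participants): men who are "engaged in regular physical activity at least three times a week for a minimum duration of one year", recruited within a sports sciences faculty.
- **When treatment is given** (Intervention, stimulation protocol): it starts one hour after the eccentric exercise, at T2.
- **What is measured:** the Procedure section says "The evaluation of muscle damage will be primarily focused on the analysis of blood CK and lactate concentrations". The named primary outcome is different: "Primary Outcome Measure: Surface Electromyography". Quadriceps strength and jump height are secondary.
- **Analysis** (Statistical analysis): a mixed ANOVA with five time points and four groups, with no term for activity between visits.

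**The concern.** The protocol treats recent exercise as a threat to accuracy at baseline, then drops that protection for the visits that carry the treatment comparison. Because treatment starts at T2, only T3, T4 and T5 are clearly post-treatment. They are three of the five time levels in the planned ANOVA.

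Two things are at stake. The first is noise: participants who exercise on different days and to different degrees add variance unrelated to recovery from the study exercise. The second is that whether and how hard to resume is each participant's own choice, made after randomisation. Someone who recovers faster may exercise sooner, and the new load could then hide part of the benefit. Since activity in this window is not recorded, neither effect could be examined afterwards.

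**Working it through.** **1. The two rules side by side.**

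| Visit | Time after muscle damage | Position relative to treatment | Rule on prior activity |
|---|---|---|---|
| T1 | before | before | none for at least 2 days |
| T2 | 1 h | treatment starts | still within day 1 |
| T3 | 24 h | after | normal activity allowed |
| T4 | 48 h | after | normal activity allowed |
| T5 | 72 h | after | normal activity allowed |

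No section limits, standardises or records activity between T2 and T5, and none explains why the baseline reason stops applying.

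**2. Expected exposure.** The input is the minimum eligible rate, 3 sessions per 7 days (Participants). Assumption: sessions are spread evenly over the week and continue at the usual rate. Expected sessions by day d = (3/7) × d.

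- By T3: 3/7 × 1 = 0.43
- By T4: 3/7 × 2 = 0.86
- By T5: 3/7 × 3 = 1.29

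Counting only the hours since T2 (23, 47 and 71) changes little: 3/168 × 23 = 0.41, 3/168 × 47 = 0.84, 3/168 × 71 = 1.27.

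If instead the three weekly sessions fall on random distinct days, the chance of at least one session is:

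- By T3: 3/7 = 43%
- By T4: 1 − 10/35 = 71%
- By T5: 1 − 4/35 = 89%

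Exposure therefore rises from visit to visit, and time is one of the two factors in the interaction being tested. These are counts of sessions, not effects on any outcome.

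**3. What extra variance would do (illustration only).** The plan's own figure comes first. For the within-between interaction, λ = f²·N·m·ε/(1 − ρ), df1 = (k − 1)(m − 1)ε and df2 = (N − k)(m − 1)ε. The Sample size section gives f = 0.20, k = 4, m = 5, ε = 1 and α = 0.05. It gives no correlation between repeated measures, so ρ = 0.5 is assumed. At N = 48, λ = 0.04 × 48 × 5/0.5 = 19.2, with df 12 and 176, and power is 0.821. At N = 44 power is 0.775, so 48 reproduces as the smallest total with equal groups. With other assumed values of ρ, power at 48 is 0.642 (ρ = 0.3), 0.728 (0.4), 0.912 (0.6) and 0.978 (0.7).

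Now suppose intervening exercise multiplies within-subject error variance by v, so that λ becomes 19.2/v. This applies v to all five time points, which is a simplification because only T3 to T5 are exposed.

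| v (assumed) | λ | Power at N = 48 | N for 80% power, equal groups |
|---|---|---|---|
| 1.00 | 19.2 | 0.821 | 48 |
| 1.10 | 17.5 | 0.774 | 52 |
| 1.25 | 15.4 | 0.705 | 60 |
| 1.50 | 12.8 | 0.604 | 68 |
| 2.00 | 9.6 | 0.457 | 92 |

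The documents give no value for v. The table shows only that the design has little slack if v is well above 1.

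**The case against.** The strongest case on the other side has five parts.

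- **Permission is not exposure.** The text allows normal activity and does not require training. Eligibility names no type of exercise or muscle group, and people made sore by 10 sets of 10 squats and two further exercises may do less than usual. This stands: T3 to T5 are open to contamination, and a reader who infers that they are contaminated goes beyond the text. It does not remove the exposure, since those who exercise more than the minimum would exceed the counts above.
- **The rules need not conflict.** A rested baseline followed by free-living recovery is a possible design. This stands in part: there is no logical contradiction. But the protocol states no such aim, and its reason for rest applies equally to CK and lactate at later visits.
- **The stated reason covers only the blood measurements.** This is correct. Extending it to quadriceps EMG, strength and jump height is an inference. It is a reasonable one, because new leg exercise loads the muscle being tested.
- **Randomisation and sham protect the comparison.** Random allocation balances prior habits on average, and the sham limits differences driven by expectation. What remains is a route through recovery itself. If treatment has no effect on recovery, that route creates no group difference, so the documents do not support a claim of false positive findings. If treatment does work, activity is partly its consequence, and the likelier result is dilution.
- **The size is unknown.** This stands. Session counts are not effect sizes, and the power table rests on assumed inflation.

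**Conclusion.** The point holds as an unexplained inconsistency with a practical cost. Activity is restricted before T1 for measurement accuracy, yet is permitted and unrecorded before every clearly post-treatment visit. At the minimum eligible exercise rate, spread evenly, about 0.4, 0.9 and 1.3 sessions per participant are expected by T3, T4 and T5. The actual figures could be lower or higher.

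The main expected harm is added variance and possible attenuation of a treatment effect. Bias is possible only where treatment changes recovery and so changes activity. A reader might infer that the follow-up data are certain to be spoiled or the group comparison invalid; the permissive wording, the random allocation and the absence of any figure for the effect of activity do not support that. The point should be fixed before enrolment, but it is not a fatal defect.

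**What to change.** Reconcile the two activity rules in the Procedure section. One consistent option is to apply the protocol's own pre-T1 restriction up to T5 as a measurement-standardisation rule. Another is to keep normal activity and state why. The choice belongs to the investigators.

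Under either option, ask at T3, T4 and T5 what exercise was done since the last visit, record it, and run a sensitivity analysis on it. Because activity after randomisation may itself be affected by treatment, that analysis should support the main comparison and not replace it.

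Cost: one question per visit. If the restriction is extended, there are also up to three more days of restricted activity per participant and possibly slightly slower recruitment.
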